### Study Objectives

#### Primary Objectives

The primary objectives of this study are as follows:

To improve current predictive models or develop new predictive models for placental dysfunction–related pregnancy complications, including preterm preeclampsia and FGR, at 2 critical gestational periods: the first trimester (11‐13 weeks) and the second trimester (26‐28 weeks)To establish third-trimester (35‐36 weeks) models to predict term preeclampsia and FGR and to define the optimal time for delivery.

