#### Primary Objectives: Prediction Model Development

Multivariable logistic regression will serve as the primary analytical approach for prediction model development at 3 gestational windows (11‐13 weeks, 26‐28 weeks, and 35‐36 weeks of gestation) to address both primary objectives 1 and 2. Clinically relevant candidate predictors are predefined and entered into multivariable models, followed by model reduction to achieve parsimony (eg, backward elimination with a retention threshold of *P*<.10). Nonlinear relationships between continuous variables and the log odds of the outcomes will be tested with the inclusion of polynomial terms up to the third degree, which will be kept in the model if statistically significant.

For each patient, this method estimates a predicted probability of developing the outcome based on the log odds of the outcome. For primary objective 1, the predicted probabilities can be used to define low- and high-risk subgroups at predefined gestational age thresholds. Specifically, a risk threshold will be defined based on clinically relevant screen-positive rates (eg, 10%, 15%, or 20%) to balance sensitivity and specificity for clinical implementation. For primary objective 2, logistic regression will similarly provide predicted probabilities. In addition, Fine and Gray competing risks time-to-event models will be used as sensitivity analyses accounting for delivery without the outcome of interest (preeclampsia or FGR) as a competing event.

To further improve upon current FMF prediction models, a Bayesian updating approach will be applied to refine existing FMF first-trimester risk estimates using additional biomarkers and clinical variables collected later in pregnancy. The FMF first-trimester risk estimate will be used as the prior probability. Likelihood ratios derived from biomarker and biophysical measurements at 26 to 28 weeks and 35 to 36 weeks will be incorporated via Markov chain Monte Carlo simulations to generate updated posterior risk distributions. This enables dynamic, individualized risk reassessment as pregnancy progresses.

All models will undergo internal validation using 5-fold cross-validation with repeated iterations to obtain stable performance estimates. Model performance will be evaluated using the following metrics:

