Model discrimination: AUC-ROC and c-statisticCalibration assessment: calibration plots and calibration slope and intercept on cross-validated dataClinical utility: sensitivity, specificity, positive and negative predictive values, and screen-positive ratesComparison against existing risk assessment methods: NICE and ACOG guidelines for preeclampsia risk scoring

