## Results

Recruitment for the Placental Health Study commenced in June 2022. By the close of recruitment in February 2026, a total of 1267 participants were enrolled. Of these, 1072 (84.6%) participants had a completed pregnancy, 144 (11.4%) participants are still to complete their pregnancy, and 51 (4%) had withdrawn or with missing or duplicated data. Comprehensive clinical data, including maternal demographics, medical and obstetric history, ultrasound measurements, Doppler indices, hemodynamic parameters, pathology laboratory results, and pregnancy outcomes, were collected through integration with electronic medical records (Table 1). Data were recorded in REDCap. Maternal serum, plasma, whole blood for RNA extraction, and urine samples have been collected and processed according to standardized operating procedures. Biospecimens are stored at −80 °C.

**Table 1. T1:** Summary of data and sample collection throughout pregnancy.

Assessment period and category	Data collected
At enrollment	
Demographic data	Date of birth, age, height, weight, BMI, ethnicity, smoking, and alcohol use status
Medical history	Diabetes mellitus, chronic hypertension, systemic lupus erythematosus, and antiphospholipid syndrome
Obstetric history	Miscarriage, termination, parity, previous preterm birth, preeclampsia, FGR^a^, placental abruption, and placenta previa
Risk assessment	Preeclampsia risk scoring (NICE^b^ and ACOG^c^ guidelines)
11‐13 weeks assessment	
First-trimester risk assessment	NIPT^d^ results (risk of trisomies, fetal sex, risk of monosomy X, sex chromosome aneuploidy risk, 22q11.2 deletion risk, and fetal fraction [cfDNA^e^, %], FGR risk, and preterm preeclampsia risk
Ultrasound and Doppler	Fetal biometry (CRL^f^ and NT^g^), fetal Doppler (ductus venosus A-wave), maternal Doppler (right and left uterine artery PI^h^ and mean PI), biophysical markers (cervical length and measurement method), and ultrasound markers (nasal bone, tricuspid regurgitation, cardiac activity, FHR^i^, holoprosencephaly, diaphragmatic hernia, atrioventricular septal defect, exomphalos, and megacystis)
BP^j^	Systolic BP, diastolic BP, and MAP^k^
Biochemical markers	Free beta-hCG^l^, PAPP-A^m^, PlGF^n^, sFlt-1^o^, and sFlt-1:PlGF ratio
Clinical pathology	Urine test, full blood count, chemistry panel, and recent iron infusion date (if available)
26‐28 and 35‐36 weeks	

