Ultrasound and Doppler	Fetal biometry (BPD^p^, HC^q^, AC^r^, FL^s^, EFW^t^, and DVP^u^); biophysical markers (cervical length and measurement method and placenta position); fetal Doppler (umbilical diastolic flow, UA^v^ PI Dopplers, MCA^w^ PI Dopplers, ductus venosus A-wave, and ductus venosus Dopplers-PIV^x^); and maternal Doppler (right and left uterine artery pulsatility index and mean PI)
Maternal hemodynamics	Systolic BP, diastolic BP, MAP, augmentation index, and maternal ophthalmic artery Doppler (right and left PI, RI^y^, EDV^z^, PSV^aa^-1, PSV-2, and PSV-2:PSV‐1)
Biochemical markers	PlGF, sFlt-1, and sFlt-1:PlGF ratio
Clinical pathology	Urine test, full blood count, chemistry panel, and recent iron infusion date (if available)
GDM screening	Random glucose, HbA_1c_^ab^, OGTT^ac^ (fasting, 1-hour, and 2-hour values); and insulin or metformin use
At delivery	
Delivery details	Gestational age at delivery; onset of labor; type of rupture of membrane; PPROM^ad^; FBS^ae^ test results; delivery type; number of vessels in cord; antenatal, intrapartum, and postnatal blood loss; postpartum hemorrhage
Neonatal outcomes	Live birth or stillbirth, onset of respirations, birth weight, birth length, head circumference, sex, Apgar scores (1 and 5 minutes), resuscitation, cord gas analysis, and SCN^af^ or NICU^ag^ admission
Maternal outcomes	BP, postpartum hemorrhage, and adverse events
All visits	
Pregnancy complication and medication	Preeclampsia, GH^ah^, antepartum hemorrhage, threatened preterm labor, FGR, PPROM, GDM^ai^; gestational age at diagnosis; medication details (start and stop date and dose)
Biological sample collection	Plasma, serum, whole blood (in PAXgene RNA blood tube), and urine

a FGR: fetal growth restriction.

b NICE: National Institute for Health and Care Excellence.

c ACOG: American College of Obstetricians and Gynecologists.

d NIPT: noninvasive prenatal testing.

e cfDNA: cell-free DNA.

f CRL: crown-rump length.

g NT: nuchal translucency.

h PI: pulsatility index.

i FHR: fetal heart rate.

j BP: blood pressure.

k MAP: mean arterial pressure.

l hCG: human chorionic gonadotropin.

m PAPP-A: pregnancy-associated plasma protein A.

n PlGF: placental growth factor.

o sFlt-1: soluble fms-like tyrosine kinase-1.

p BPD: biparietal diameter.

q HC: head circumference.

r AC: abdominal circumference.

s FL: femur length.

t EFW: estimated fetal weight.

u DVP: deepest vertical pocket.

v UA: umbilical artery.

w MCA: middle cerebral artery.

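### The FGR models have no FGR-relevant benchmark: the only comparators named for any model are the NICE and ACOG preeclampsia risk scores

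*Protocol article*

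**What the plan says.** The Primary Objectives section makes FGR a target in every window. The first objective covers "placental dysfunction–related pregnancy complications, including preterm preeclampsia and FGR, at 2 critical gestational periods" (11-13 and 26-28 weeks). The second, at 35-36 weeks, calls for "models to predict term preeclampsia and FGR and to define the optimal time for delivery".

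Primary Objectives: Prediction Model Development then sets out how performance is judged. It introduces a single list of metrics with "All models will undergo internal validation using 5-fold cross-validation with repeated iterations to obtain stable performance estimates". The last item in that list is the comparison with "existing risk assessment methods: NICE and ACOG guidelines for preeclampsia risk scoring". There is no separate list by outcome or by window.

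Table 1 in the Results shows what is on file. At 11-13 weeks the first-trimester risk assessment includes "FGR risk, and preterm preeclampsia risk". At 26-28 and 35-36 weeks the scan records abdominal circumference (AC) and estimated fetal weight (EFW). Textbox 1 defines FGR largely through centiles of these two measures, with Doppler and growth-crossing criteria added.

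**The concern.** The first primary objective is to improve current models or develop new ones, and the Discussion says the gain is to come from added Doppler, hemodynamic and angiogenic markers. For FGR, a claim of improvement needs a reference that predicts FGR. A checklist built to score preeclampsia risk is not such a reference.

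Two things are at stake. First, a gain over the checklist would not show whether the new markers add anything to a fetal-size measurement the clinic already has. If EFW or AC is among the predictors, size alone could produce the gain. Second, the references that could answer the question are already in the dataset, but the plan does not use them as comparators.

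**Working it through.** **Step 1: is any FGR comparator named elsewhere in the article?**

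| Place | What it offers | FGR benchmark? |
|---|---|---|
| Abstract, Methods | A general commitment to compare with existing approaches | None named |
| Prediction Model Development, metrics list | NICE and ACOG scores | Preeclampsia only |
| Prediction Model Development, Bayesian updating | Fetal Medicine Foundation (FMF) first-trimester risk | Used as a prior, not listed as a comparator |
| Secondary Objective Analysis, objective 2 | Performance of each biomarker on its own | No model-versus-centile comparison |
| Introduction and Discussion | FMF detection rates for small for gestational age: 56% early, 46% preterm | Background only |
| Table 1 | First-trimester FGR risk; EFW and AC at the two later visits | Recorded, not assigned as comparators |

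The metrics list is therefore the only place that names a comparator, and what it names is specific to preeclampsia.

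**Step 2: which reference exists in each window?**

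- 11-13 weeks: the biometry is crown-rump length and nuchal translucency, so there is no EFW or AC centile. The recorded first-trimester FGR risk is the available reference.
- 26-28 and 35-36 weeks: the EFW or AC centile from the visit scan.

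**Step 3: the plan's own planning figure.** Sample Size Estimation gives 10% incidence, up to 15 predictors, AUC 0.75 and about 1700 participants. An AUC of 0.75 at 10% prevalence corresponds to a Cox-Snell R² of 0.0748 (by simulation). With a target shrinkage of 0.9 (an assumption; the article does not state it):

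n = 15 / [(0.9 − 1) × ln(1 − 0.0748/0.9)] ≈ 1729,

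which is within 3% of 1700. The figure reproduces. The point made here does not depend on it; 0.75 serves below only as a reference level.

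**Step 4: how well might fetal size alone do? (illustration)** The documents give no correlation between size at a visit and later size, so a range is assumed. Size z scores at the two times are bivariate normal, with 2,000,000 draws. The AUC is that of the visit z score alone.

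| Assumed correlation | Later size <10th centile | Later size <3rd centile |
|---|---|---|
| 0.3, all fetuses | 0.66 | 0.69 |
| 0.3, fetuses <10th at visit removed | 0.64 | 0.66 |
| 0.5 to 0.8, all fetuses | 0.77 to 0.92 | 0.81 to 0.95 |
| 0.5 to 0.8, fetuses <10th at visit removed | 0.73 to 0.88 | 0.76 to about 0.9 |

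At correlations of about 0.5 and above the centile alone mostly exceeds 0.75; at weak correlations it does not. Removing fetuses that are already small lowers every figure, so the choice of comparison population matters. The simulated outcome is later size only, whereas Textbox 1 also uses Doppler and growth-crossing criteria.

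**Step 5: could the checklist comparison mislead? (illustration)** Assumed AUCs for FGR are 0.70 for the model, 0.60 for the checklist and 0.80 for the centile, with marker correlation 0.3 and 500 simulated studies. N = 1072 completed + 144 active = 1216. The FGR case counts are also assumed.

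| FGR cases | Model significantly beats checklist | Model significantly worse than centile |
|---|---|---|
| 60 | 61% | 76% |
| 120 | 90% | 96% |

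The ordering of the three AUCs is an input here. The table shows only that a win over the checklist gives no information about the comparison that matters.

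**The case against.** The strongest reply is that the comparator item limits itself to preeclampsia by its own wording. The article nowhere says that FGR models will be set against these checklists, or that beating them will count as better FGR prediction. On that reading the FGR comparator is simply not spelled out, and a condensed article may leave such detail to a fuller plan. The first part stands: the plan does not state that an FGR model will be credited for beating a preeclampsia score. The second part does not dispose of the point. The article contains its own analysis plan, names its comparators under a list introduced for all models, and names none that fits one of its two primary outcomes.

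A reader might also infer that an FGR model worse than the fetal-size centile could be reported as an advance. That needs EFW and AC to be left out of the model, and the article does not say they will be. The Introduction's examples of predictors do not include fetal size, but the Introduction also plans to integrate biophysical parameters, and the Discussion mentions routine antenatal measurements. A model containing the centile would not normally discriminate materially worse than the centile alone, apart from overfitting. In that case the remaining harm is that the markers' added value goes unreported.

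Three further objections are fair. The FMF risk is available before and after Bayesian updating, so existing methods are not ignored, although no head-to-head comparison with that risk is listed. The correlations and AUCs in the illustrations come from no document. And because the size centile is part of the FGR definition, using it as a comparator without excluding fetuses that already qualify would let it partly predict itself; the fix has to deal with this.

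**Conclusion.** The concern holds in this form: as written, no FGR-relevant benchmark is fixed for any of the three windows, and the only named comparators score a different disease. The plan therefore cannot support a claim that the added markers improve FGR prediction over what is available. This follows from the text alone and rests on no assumed number.

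The size of the consequence is not established. The AUC ranges and simulated percentages depend on assumed correlations, comparator AUCs and case counts, and should be read as illustrations. The argument about the size centile applies at 26-28 and 35-36 weeks only; at 11-13 weeks the unused reference is the recorded FGR risk. The documents do not support the stronger statement that an FGR model inferior to the routine scan will be presented as superior. The point merits a change to the plan because the remedy uses data already recorded and the primary publications are still to come.

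**What to change.** In the performance list of Primary Objectives: Prediction Model Development:

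1. Limit the NICE and ACOG comparison to the preeclampsia models.
2. Give the FGR models their own comparator, evaluated in the same women: the recorded first-trimester FGR risk at 11-13 weeks, and a model with the EFW or AC centile alone at 26-28 and at 35-36 weeks.
3. Make the two later comparisons among pregnancies that do not already meet the Textbox 1 definition at that visit (early-onset criteria at 26-28 weeks, late-onset criteria at 35-36 weeks).
4. Report the cross-validated difference in AUC, and the difference in detection at the same screen-positive rate (the article already gives 10%, 15% and 20% as examples), each with a confidence interval.

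The cost is a little more analysis and no new data collection. The apparent gain for FGR will probably look smaller, and the exclusion in item 3 leaves fewer FGR cases, so the intervals in the later windows will be wider.

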#### Secondary Objective Analysis

For secondary objective 1, time-to-event analyses will be used to evaluate the association between predicted risk scores and adverse maternal and perinatal outcomes after diagnosis of complications. For secondary objective 2, AUC-ROC analysis, sensitivity and specificity, and predictive values will be used to assess the individual predictive performance of each biomarker candidate. For secondary objective 3, longitudinal biomarker trajectories will be compared between participants with the outcomes of interest and those without these outcomes using linear mixed-effects models with random intercepts and slopes for each participant. Exploratory proteomics and metabolomics analyses will be performed on a subset of samples to identify novel biomarkers and biological pathways associated with placental dysfunction.

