**Methods:**

The Placental Health Study is a prospective cohort study conducted at the Maternal Fetal Medicine Unit at Gold Coast University Hospital, Australia. Singleton pregnancies are enrolled at 11 to 13 weeks, 26 to 28 weeks, and 35 to 36 weeks of gestation and are followed until delivery. Exclusion criteria are multiple pregnancies, major fetal anomalies, maternal age below 18 years, and inability to provide informed consent. Clinical data, standardized ultrasound and Doppler measurements, hemodynamic parameters, and biospecimens (serum, plasma, whole blood RNA, and urine) are collected at each visit. Three gestational age-specific datasets (11‐13 weeks, 26‐28 weeks, and 35‐36 weeks) will be constructed for model development. Prediction models will be developed using multivariable logistic regression. Competing risks (Fine and Gray) models will be used as sensitivity analyses for outcomes related to gestational age at delivery. Bayesian updating will be applied to refine existing Fetal Medicine Foundation risk estimates using additional biomarkers or variables collected later in pregnancy. Developed models will undergo internal validation via 5-fold cross-validation, with performance assessed through model discrimination, calibration, and comparison against existing approaches. Collected biospecimens will also be analyzed for angiogenic markers and exploratory omics studies.

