#### Secondary Objectives

The secondary objectives are as follows:

To predict the outcomes and prognosis of placental dysfunction–related complications by applying the developed predictive modelsTo evaluate the predictive value of clinically tested pregnancy biomarkers for pregnancy outcomes related to placental dysfunctionTo investigate placental biological processes and their role in generating maternal circulating biomarkers associated with preeclampsia and FGR, thereby enhancing the understanding of uteroplacental dysfunction pathophysiology

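### Secondary objective 1 applies time-to-event analysis to outcomes decided at birth, so a cause-specific hazard ratio would mix prognosis with speed of delivery

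*Protocol article*

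**What the plan says.** The objective (Secondary Objectives) begins "To predict the outcomes and prognosis of placental dysfunction" and concerns complications already diagnosed. The section Secondary Objective Analysis gives it one class of method for all outcomes: "time-to-event analyses will be used to evaluate the association between predicted risk scores and adverse maternal and perinatal outcomes after diagnosis of complications". No model, effect measure, time scale, outcome list or treatment of delivery is named for it.

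The Abstract (Methods) says that participants "are followed until delivery". Table 1 in Results lists what is collected at delivery:

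- Neonatal: "Live birth or stillbirth, onset of respirations, birth weight, birth length, head circumference, sex, Apgar scores (1 and 5 minutes), resuscitation, cord gas analysis", followed by special care nursery or neonatal intensive care admission.
- Maternal: "BP, postpartum hemorrhage, and adverse events". No event dates are listed.

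Table 1 also records gestational age at diagnosis of complications and gestational age at delivery. Its block for all visits lists complications that can arise before birth, such as antepartum hemorrhage.

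Competing-risk handling appears in Primary Objectives: Prediction Model Development. There, Fine and Gray models are a sensitivity analysis for onset of preeclampsia or fetal growth restriction, with delivery free of the outcome as the competing event. Nothing extends this to secondary objective 1.

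**The concern.** An Apgar score, a cord gas result, a neonatal admission or a postpartum hemorrhage cannot occur before birth. For such an outcome the clock that starts at diagnosis stops at delivery whether or not the outcome is adverse. The time axis measures how long the pregnancy continued after diagnosis, which depends on gestational age at diagnosis and on delivery decisions. It does not measure how soon harm came.

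A woman delivered without the outcome can no longer have it. If she is counted as censored, the resulting hazard ratio compares events per day of continuing pregnancy, while the prognostic question is how many affected pregnancies end badly. Two groups with the same proportion of adverse outcomes then differ in hazard merely because one is delivered sooner. The answer to objective 1 could be too large, too small or of the wrong sign.

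**Working it through.** The article gives no figure for this objective, so there is nothing of its own to reproduce. The check is of the mechanism, under declared assumptions.

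**Inputs**
- From the article: time starts at diagnosis, follow-up ends at delivery, and most neonatal outcomes are fixed at birth.
- Assumed: a binary score (high or low); risk of the adverse outcome 20% with a low score and 20%, 30% or 40% with a high score; exponential diagnosis-to-delivery intervals; risk at birth that does not depend on the length of the interval, given the score. The delivery-rate ratio D (high over low score) is varied from 0.33 to 3, so both directions are shown.

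**Formula.** If every event happens at delivery, the cause-specific hazard in group g is (delivery rate in g) × (risk at birth in g). Therefore

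HR = D × RR, where RR = p1/p0.

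The sign reverses when D < 1/RR: below 0.67 for RR 1.5 and below 0.5 for RR 2.0.

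**Numbers.** For RR = 0.30/0.20 = 1.5, by formula: 0.33 × 1.5 = 0.495; 0.5 × 1.5 = 0.75; 2 × 1.5 = 3.0; 3 × 1.5 = 4.5. A simulation of 400,000 diagnosed women, with delivery without the event censored, gave these cause-specific hazard ratios:

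| D | RR 1.0 | RR 1.5 | RR 2.0 |
|---|---|---|---|
| 0.33 | 0.33 | 0.49 | 0.65 |
| 0.5 | 0.50 | 0.75 | 1.00 |
| 0.67 | 0.68 | 1.01 | 1.33 |
| 1 | 1.01 | 1.48 | 2.00 |
| 1.5 | 1.52 | 2.23 | 3.01 |
| 2 | 2.01 | 3.02 | 4.04 |
| 3 | 3.01 | 4.52 | 5.95 |

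With no prognostic effect at all, the hazard ratio simply equals D. The same data analysed as risks give the true RR at every D, apart from simulation error; for 30% against 20% the odds ratio is (0.30/0.70)/(0.20/0.80) = 1.71.

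**Alternative model.** A Fine and Gray model on the same data, with delivery without the event as the competing event, gave subdistribution hazard ratios of 1.49 to 1.71 for RR 1.5 and 2.08 to 2.45 for RR 2.0. There was no reversal.

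**Events before birth.** An illustrative mix gave high-score women 1.5 times the antepartum event hazard, with D = 0.5. As antepartum events replaced birth events, the cause-specific hazard ratio went from 0.76 (all at birth) through 0.97 and 1.18 to 1.51 (all antepartum), recovering the 1.5 built in. With all events antepartum and D = 2, it was 1.47 while the plain risk ratio was 0.77, because faster delivery shortens time at risk. For events before birth, time matters and a risk comparison alone would mislead.

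**The case against.** The strongest reply is that the article names only a class of method. It fixes no Cox model, hazard ratio or censoring rule, and a condensed article may leave these to a fuller plan. The authors know the competing-event structure, since they use Fine and Gray models elsewhere, and such a model showed no reversal. The objective also covers stillbirth and maternal events that can precede delivery, for which time-to-event analysis is legitimate. Gestational age at diagnosis could be a covariate in a time-to-event model too.

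Much of this stands. A reader might infer that the planned analysis will mainly measure delivery speed, or will show high-score women as protected. The documents do not support that. No hazard ratio is specified, no intervals or risks are given, and nothing shows that high-score women are delivered more slowly; if they are delivered faster, the error is inflation.

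It does not remove the point. The class of method is stated for all the outcomes, and it does not fit those fixed at birth. The competing-event handling is stated only for onset of preeclampsia or fetal growth restriction. Where all events occur at birth, Fine and Gray keeps the right direction only because it approximates the risk comparison that a binary model gives directly. Adjusting for gestational age at diagnosis removes only the part of the difference in delivery speed that it explains; within a given gestational age, HR = D × RR still applies.

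**Conclusion.** The concern holds in limited form. For outcomes determined at or just after birth, the stated method class does not suit the question. If delivery without the event is censored, the hazard ratio is the risk ratio multiplied by the delivery-rate ratio. With an assumed RR of 1.5 it ranges from about 0.5 to 4.5 for D between 0.33 and 3, and it is correct only at D = 1. Reversal is a possibility that requires high-score women to be slower to deliver by a factor greater than the RR; it is not a prediction.

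These sizes rest on assumed risks, exponential intervals and events occurring only at delivery. They do not carry over to antepartum events, so the objective as a whole is not invalid. No primary analysis is affected.

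**What to change.** Split the outcomes of secondary objective 1 in the analysis plan.

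1. **Determined at or after birth** (Apgar scores, resuscitation, cord gases, special care or intensive care admission, postpartum hemorrhage): use logistic or risk regression of each outcome on the predicted risk score among diagnosed women, with gestational age at diagnosis as covariate. Report risk ratios or risk differences.
2. **Dated antepartum events** (for example stillbirth, antepartum hemorrhage): keep time-to-event methods, with delivery without the event as a competing event. State which events have a usable date; Table 1 lists stillbirth only as a status at delivery.
3. **Diagnosis-to-delivery interval**: if it is of interest, analyse it as a separately labelled time-to-event outcome.

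The cost is plan wording. Gestational age at diagnosis and at delivery are already collected, so birth-determined outcomes need no new data. The small downside is that they will have no hazard ratios.
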